# Antiviral treatment in adult patients hospitalized for influenza: study protocol for a multi-center, randomized, placebo-controlled trial on the efficacy of baloxavir marboxil to reduce time to clinical improvement and the risk for severe complications (the INFLUENT trial)

**DOI:** 10.1186/s13063-025-09248-0

**Published:** 2025-11-24

**Keywords:** Influenza, Flu, Antiviral, Treatment, Hospitalization, Adult, Randomized, Clinical trial

## Abstract

**Background:**

Seasonal influenza virus leads to more than half a million deaths each year worldwide. Due to its capacity to evolve, it is considered the most likely pathogen to cause a future pandemic. Antiviral treatment options are currently limited, with the most widely used drugs being neuraminidase inhibitors and the cap-dependent endonuclease inhibitor baloxavir marboxil. In adult hospitalized patients, due to the lack of placebo-controlled trials, current available evidence on antiviral treatment benefits is essentially based on observational studies. A placebo-controlled clinical trial is needed to fill this knowledge gap.

**Methods:**

This is an investigator-initiated, randomized, triple-blind, placebo-controlled, superiority, multi-center trial to assess the clinical efficacy of single-dose baloxavir in decreasing time to clinical improvement in adult immunocompetent patients hospitalized with influenza. Patients (*n* = 484) with confirmed, severe infection (NEWS2 score ≥ 4) will be recruited over three influenza seasons in four large Swiss hospitals. Primary outcome: time to clinical improvement (in hours), calculated from treatment administration until NEWS2 score ≤ 2 maintained for 24 h or until hospital discharge, whichever comes first. The primary outcome is calculated in all patients independently of the duration of symptoms at treatment administration, as well as in participants treated early (<72 h) post onset of symptoms. The main secondary outcomes are the risk of serious influenza complications, length of hospitalization, and difference in viral load at D3 post-treatment administration.

**Discussion:**

This trial’s results, whether positive or negative, will impact clinical guidance. If baloxavir’s clinical benefit is demonstrated, a single-dose pill would be the easiest implementable treatment option in case of large seasonal outbreaks or a new influenza pandemic. If a clear treatment benefit is not shown, antiviral treatment administration in the hospitalized patient population could be reconsidered to prevent unnecessary medication, lower the risk of resistance development linked to treatment overuse, and ultimately save unnecessary treatment-related expenses.

**Trial registration:**

ClinicalTrials.gov NCT06653569. Registered on October 22, 2024, 
https://clinicaltrials.gov/study/NCT06653569?term=NCT06653569&rank=1.

**Supplementary Information:**

The online version contains supplementary material available at 10.1186/s13063-025-09248-0.

## Introduction

### Background and rationale {6a}

Each year, influenza causes a severe disease burden worldwide. Every winter in Switzerland, several thousands of patients require hospitalization due to complicated influenza, with hundreds of deaths [1]. Treatment strategies contributing to a shorter hospital stay as well as to a lower risk of complications have major public health importance.

In addition, due to its immense capacity to evolve, influenza is one of the leading causes of human pandemics of respiratory origin [2]. The avian influenza A(H5N1) strains causing the epizootic ongoing since 2020 are not yet adapted to humans. However, each new spillover increases the risk of mutations allowing adaptation to the mammalian host [3]. Determining the best possible use of antiviral treatment resources will be crucial in case of a new pandemic.

The most frequently used antiviral drugs to treat influenza in hospitalized patients are neuraminidase inhibitors (NAI) including oseltamivir and the cap-dependent endonuclease inhibitor baloxavir marboxil (baloxavir from thereof). For uncomplicated cases in high-risk outpatients, a 16-to-25-h reduction in symptom duration was observed when oseltamivir was administered within 48 h post onset of symptoms (POS) [4–6].

Importantly, no placebo-controlled trial on influenza antivirals in adult hospitalized patients has ever been published [5]. Current available evidence is based on a series of observational studies and their systematic reviews. Most of them identify treatment timing as an important factor modulating potential efficacy. In two retrospective analyses of patient data during the influenza A(H1N1) pandemic, early (≤48 h POS) oseltamivir treatment was associated with lower mortality risk (aOR 0.50, 95% CI 0.37, 0.67) as well as with shorter in-hospital stay (−1.19 day, IQR −0.85, −1.55) [7, 8]. Late oseltamivir treatment benefits (>48 h POS) were only shown in patients requiring intensive care upon admission (mortality risk OR 0.65, 95% CI 0.46, 0.93) [7]. Some of these findings have been criticized for high risk of survival and selection bias, confounding by disease severity, as well as for industry funding [4, 9]. A recently published large retrospective study demonstrated an 18% decrease in 30-day mortality risk associated with oseltamivir treatment in patients infected with influenza A, but not with influenza B. The association remained significant when antiviral was administered ≥48 h after hospitalization [10]. Another study showed an association between prompt antiviral treatment at hospitalization and 30-day mortality risk decrease when compared to delayed treatment administration (treatment on day 1: aOR 1.14, 95% CI 1.01, 1.27; between days 2 and 5: aOR 1.40, 95% CI 1.17, 1.66) [11].

On the other hand, a recent systematic review and network meta-analysis of randomized controlled trials in children and adults, comparing NAI treatment to placebo (in children)/to standard of care or to each other (in adults), highlighted the uncertainty of the efficacy of NAI to lower the risk of mortality (risk difference: −18 to +4/1000) or admission to ICU, and concluded that treatment may shorten the duration of hospitalization (for oseltamivir: −1.63 days (95% CI: −2.81 to −0.45) (low level of evidence)) [12, 13]. In hospitalized patients, there is only one retrospective observational study assessing the clinical benefits of baloxavir, showing a significant 30-day all-cause mortality reduction in the baloxavir group compared to oseltamivir when treatment was administered within 48 h POS [14]. Combination antiviral therapies (baloxavir and NAI) could in theory increase clinical effectiveness via the cumulation of antiviral potency (additive or synergistic effects) as well as by reducing the risk of antiviral resistance [15]. However, one phase III multi-center randomized clinical trial in hospitalized adult patients failed to show a benefit in time to symptom alleviation when compared to NAI monotherapy [16]. Due to the lack of strong evidence, physicians remain divided over whether patients hospitalized with complicated influenza would benefit from antiviral administration and, if yes, for how long after symptom onset.

As the equipoise exists regarding treatment efficacy, a placebo-controlled trial is needed to fill in this knowledge gap.

### Objectives {7}

Primary objective: To measure the clinical efficacy of single-dose baloxavir in shortening the time to clinical improvement compared to placebo in adult immunocompetent patients hospitalized for influenza irrespective of the duration of symptoms.

Co-primary objective: To measure the clinical efficacy of single-dose baloxavir in shortening the time to clinical improvement compared to placebo in the subgroup of adult immunocompetent patients hospitalized for influenza and treated less than 72 h POS. Secondary objectives: To assess baloxavir’s efficacy in decreasing the risk for and the duration of oxygen therapy related to the influenza episode, as well as its efficacy in preventing serious influenza-related complications; to measure its effects on viral-load kinetics including duration of infectiousness.

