### Intervention description {11a}

A total of 484 participants will be included, with 242 randomized in each arm. In the treatment arm, participants will receive baloxavir marboxil (Xofluza®) according to their body weight (<80 kg: 1 tablet of 40 mg PO as a single dose, ≥80 kg: 2 tablets of 40 mg PO as a single dose). Participants randomized to the placebo arm will receive one single dose of placebo. The number of placebo capsules will be adapted to the patient’s weight (<80 kg: 1 capsule, ≥80 kg: 2 capsules).

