#### Secondary clinical outcomes

Clinical status severity score (from 1 to 6) on day 7 post-treatment administrationDuration of hospitalization post-treatment administration (in hours)Duration of O_2_ supplementation post-treatment administration (in hours)In-hospital clinical failure, defined as death or ICU or intermediate care unit (ICMU) admission during hospitalization or up to 30 days post-treatment administration in case of prolonged hospital stayMortality at D90Influenza-related complications occurring between D0 and D90, diagnosed by the treating physician (composite outcome defined as pneumonia, sepsis, acute lung injury or acute respiratory distress syndrome (ARDS), encephalitis/encephalopathy, myo- or pericarditis, otitis, sinusitis as well as any cardiovascular event (cardiac decompensation, myocardial infarction, or stroke))Number of antibiotic days (AD) prescribed during hospitalization or up to 30 days post-treatment administration in case of longer hospital stayQuality of life at day 90 post-treatment administration. Questionnaire type: EQ-5D-5L

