### Sample size {14}

Our hypothesis is that baloxavir treatment in adult, immunocompetent patients hospitalized for influenza will shorten the time to clinical improvement by at least 36 h compared to placebo. This 36-h difference was chosen as the minimal time difference considered to have a meaningful impact on clinical care. The median time to clinical improvement, in patients who received antivirals in a large clinical study, was about 4 days (97.5 h) [16]. The addition of the 36-h difference equals a time to clinical improvement of 5.5 days in the placebo group.

Two sample size calculations were performed. Sample size calculation no. 1 concerns all patients hospitalized for influenza (regardless of symptom duration at treatment administration): under the constant and proportional hazard assumption, median times to clinical improvement of 5.5 days in the placebo group and 4 days in the baloxavir group correspond to a hazard ratio of 1.375. With a follow-up period of 30 days, we calculated that a total number of 432 participants (216 per arm) would provide the trial with at least 90% power to detect such a baloxavir effect on time to clinical improvement at a two-sided significance level of 0.05.

Sample size calculation no. 2 concerns the subgroup of patients hospitalized for influenza with symptoms evolving for less than 72 h: under similar hypothesis (median times to clinical improvement of 5.5 days in the placebo group and 4 days in the baloxavir group, corresponding to a hazard ratio of 1.375 under the constant and proportional hazard assumption, and a follow-up period of 30 days), we calculated that a sample of 161 patients per arm would provide 80% power to detect a baloxavir effect in a subgroup analysis, at a two-sided significance level of 0.05. Assuming two out of three patients will present symptoms evolving for less than 72 h (ratio of 2:1), the study will need to include a total of 484 patients. With that sample size, the study will reach a power of 93% in the general population of hospitalized patients.

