## Data collection and management

### Plans for assessment and collection of outcomes {18a}

Primary outcome: We use the NEWS2 scoring system as a reliable and easily implementable method to evaluate disease severity at inclusion and to measure improvement in clinical status during follow-up. The primary outcome (NEWS2 score or hospital discharge) is recorded in the CRF once a day by dedicated study nurses. Components of the NEWS2 score are part of regular clinical management and therefore recorded by the team in charge of the patient during hospitalization. Death or ICU admission is not considered as discharge in the context of the primary endpoint. In case the patient is transferred to another hospital, it is considered as discharge regarding the primary endpoint. Transfers from the four participating university centers most often occur to rehabilitation hospitals, indicating that the patient no longer requires acute care for the influenza episode and is thus considered discharged.

To evaluate change in clinical status following treatment, we also use the 6-point ordinal clinical status severity scale. The remaining clinical outcomes include parameters which are easily measurable (need for O_2_ supplementation) or easily evaluable (need for antibiotic therapy for influenza complication, ICU admission, death). Influenza complications are retrieved from the discharge letter at the end of the hospital stay. The study nurses/physician collect the above data directly from the patients’ electronic medical records and enter it into the e-CRF. Clinical monitors will randomly check for data consistency and correctness.

Quality of life questionnaire EQ-5D-5L [17, 18] is filled out by the study nurses/physician on D0 and D90 post-treatment administration. At D90, the answers are collected by the study nurses/physician via the phone and are entered directly to the e-CRF. In case the patient is incapable of answering the questions, the questionnaire is not filled out.

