#### Clinical secondary outcomes

Status severity score at day 7 will be compared between groups using a Cochran-Mantel-Haenszel test stratified on center.

Length of stay (from treatment administration to hospital discharge) and duration of O_2_ supplementation will be compared between groups using a linear regression model adjusted on center. The Huber-White method will be used to compute a robust variance estimator of the coefficients. Depending on the number of deceased patients, competitive risk analyses may be preferred to a linear regression model. Risk of in-hospital clinical failure will be compared between groups using a Cochran-Mantel-Haenszel test stratified on center. Risk difference and relative risk stratified on center will be estimated using the Mantel-Haenszel method.

Mortality and risk of influenza-related complications at day 90 will be compared between groups using a Cochran-Mantel-Haenszel test stratified on center. Risk difference and relative risk stratified on center will be estimated using the Mantel-Haenszel method.

Mean number of antibiotic days (AD) for respiratory illness will be compared between groups using a linear regression model adjusted on center.

Quality-of-life score at D90 will be compared between groups using a linear regression model adjusted for center and quality-of-life score at baseline.

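### The secondary objective covers both the risk and the duration of oxygen therapy, but only duration is defined and analysed, so the risk part has no test

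*Protocol article*

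**What the plan says.** Objectives {7} gives a two-part oxygen aim among the secondary objectives: "efficacy in decreasing the risk for and the duration of oxygen therapy related to the influenza episode".

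The list of secondary clinical outcomes has one oxygen entry, "Duration of O_2_ supplementation post-treatment administration (in hours"). The methods for clinical secondary outcomes analyse that entry alone: "duration of O_2_ supplementation will be compared between groups using a linear regression model adjusted on center", with a robust variance. Depending on the number of deaths, a competing-risk analysis may replace the regression.

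The section on assessment and collection of outcomes {18a} mentions oxygen need as something recorded: "The remaining clinical outcomes include parameters which are easily measurable (need for O_2_ supplementation"). No outcome or test is built on it.

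The eligibility criteria exclude high-flow oxygen, non-invasive ventilation and long-term home oxygen. They do not exclude conventional oxygen at entry.

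**The concern.** An objective about risk needs an outcome that counts who starts oxygen. Hours of oxygen do not do that. Two groups contribute to the duration comparison. Patients already on oxygen at dosing can only have its use shortened. Patients not on oxygen can have it prevented. One difference in hours combines the two effects.

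A shorter duration could therefore come from either route, and a null result could hide fewer patients starting oxygen. Followed as written, the plan reports on duration and says nothing separate about risk. An analysis of risk added after unblinding would be post hoc.

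**Working it through.** **1. Does any other outcome cover the risk of oxygen?** The outcomes compared as risks are:

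- clinical failure, "In-hospital clinical failure, defined as death or ICU or intermediate care unit (ICMU) admission during hospitalization" (with a limit of 30 days for long stays), which does not include oxygen;
- mortality at day 90, which does not include oxygen;
- influenza-related complications to day 90, a list of diagnoses in which starting oxygen does not appear.

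The six-point score is a status on day 7 only. Its categories are not given in the article, so whether it has an oxygen level is unknown. Even if it has one, a status on one day does not count patients who started oxygen and stopped before then. The mismatch therefore stands without any arithmetic.

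**2. How much can it matter?** The article gives no figure for any oxygen outcome, so there is none to reproduce.

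*Inputs from the article:* "A total of 484 participants will be included, with 242 randomized in each arm", and testing as for the primary outcome "at a two-sided significance level of 0.05".

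*Assumptions, none of them in the article:* a share f is on oxygen at dosing. The rest start oxygen with risk p0 (placebo) or p1 (baloxavir). Hours among users are exponential with mean m, and never-users count as 0 h. Center adjustment is ignored.

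*Mean comparison.* The share using any oxygen is q = f + (1 − f)p. The mean is qm and the variance is m²q(2 − q). With f = 0.5, p0 = 0.30, p1 = 0.15 and no effect on duration:

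- q0 = 0.65 and q1 = 0.575, so the difference is 0.075m.
- Variances are 0.8775m² and 0.8194m², so SE = m√((0.8775 + 0.8194)/242) = 0.0837m.
- z = 0.075/0.0837 = 0.90, and power = Φ(0.90 − 1.96) ≈ **14%**.

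Here m cancels. With m = 72 h the means are 46.8 h and 41.4 h, a fall of 12%. If new starters average 48–120 h and baseline users 72–96 h, power is 7–25%.

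*Risk comparison* among 242 × 0.5 = 121 per arm not on oxygen at dosing:

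- The null SE is √(2 × 0.225 × 0.775/121) = 0.0537. The SE under the alternative is √((0.21 + 0.1275)/121) = 0.0528.
- Power = Φ((0.15 − 1.96 × 0.0537)/0.0528) ≈ **80%**, or 81% with the unpooled SE throughout.

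*If hours also shorten.* Let baloxavir users average m/1.375 = 0.727m. This borrows the hazard ratio of the sample size section, which is itself an assumption for oxygen hours. The baloxavir mean becomes 0.575 × 0.727m = 0.418m and its variance 0.8194m²/1.375² = 0.4334m². The difference is 0.232m, SE = m√((0.8775 + 0.4334)/242) = 0.0736m, z = 3.15 and power ≈ **88%**.

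**3. Range, by the same formulas (power):**

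| On oxygen at dosing | New need | Mean, no effect on duration | Mean, hours ÷ 1.375 | Risk comparison |
|---|---|---|---|---|
| 0% | 30% vs 20% | 39% | 82% | 72% |
| 0% | 30% vs 15% | 75% | 96% | 98% |
| 30% | 30% vs 20% | 15% | 80% | 57% |
| 30% | 30% vs 15% | 28% | 89% | 91% |
| 50% | 30% vs 20% | 9% | 82% | 43% |
| 50% | 30% vs 15% | 14% | 88% | 80% |
| 70% | 30% vs 20% | 5% | 86% | 28% |
| 70% | 30% vs 15% | 7% | 89% | 58% |

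For a pure effect on risk, the mean is the weaker test in every row. Once duration shortens as well, the gap narrows or reverses.

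**The case against.** A reader might infer that the duration analysis barely responds to a benefit on oxygen need and that a real effect would be buried. The article does not support that. The low power figures need an effect on risk with none on duration, whereas the trial's hypothesis is faster recovery. If hours shorten too, the mean comparison has 80% power or more in every row of the table. This objection stands. What it does not repair is interpretation: a significant difference in hours still would not say whether fewer patients needed oxygen.

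A reader might also take it as stated that the regression covers all patients with never-users at zero hours. That is the natural reading of a comparison between groups with no restriction, but the text does not say so. A condensed article may leave the handling of never-users to the full protocol or the analysis plan. The power figures depend on it, but the missing risk outcome does not.

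Nor is the objective beyond rescue. The data appear to be collected, so a proportion can be reported. Oxygen is also absent from the main secondary outcomes named in the abstract, which limits the weight of the point. Finally, the added risk test would have modest power in some settings (28% in the worst row), so a null result on it could be over-read as well.

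The possible competing-risk analysis concerns how deaths affect duration. It does not supply a test of starting oxygen.

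**Conclusion.** The concern holds as a mismatch between a stated secondary objective and the outcomes and analyses meant to serve it. Half of the oxygen objective has no outcome and no test. This is more than detail left to the analysis plan, because the article's outcome list and methods both deal with oxygen and name only duration.

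Its size is uncertain. About 14% vs 80% power applies to a pure risk effect with half the patients on oxygen at dosing, a halving of new need and zero hours for never-users. The gap is smaller if few are on oxygen at dosing, and the order reverses (about 88% vs 80–81%) if hours also fall by a factor of 1.375. The firm conclusion is that the planned comparison cannot separate prevention from shortening. It does not follow that the comparison is always insensitive. The primary outcome and the sample size are not affected.

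**What to change.** Add to the secondary clinical outcomes the proportion of patients starting supplemental oxygen after dosing, in hospital and up to day 30, among those not on oxygen at dosing. Compare it by the center-stratified Cochran-Mantel-Haenszel test, with Mantel-Haenszel risk difference and relative risk, as already planned for the other risks. Keep duration as a separate outcome, state which patients it covers and how never-users are counted, and adjust it for oxygen use at dosing.

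At minimum, if no risk outcome is wanted, remove the risk aim from the objective so that objective, outcome and analysis agree.

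The cost is one more secondary test, apparently on data already recorded, with limited power if most patients are on oxygen at dosing. Recruitment is planned to run through the 2026/2027 season, so the change can be made before unblinding.

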### Trial design {8}

This is an investigator-initiated, randomized, triple-blind, placebo-controlled, parallel group, superiority, multi-center trial with an allocation ratio of 1:1.

## Methods: participants, interventions and outcomes

### Study setting {9}

The trial is implemented in four large Swiss hospitals: Geneva University Hospitals; University Hospital Zurich; University Hospital Lausanne; Locarno and Lugano Regional Hospitals.

